### Study Protocol

#### Setting

The study will be conducted at two EDs in Providence, Rhode Island: Rhode Island Hospital (RIH), a tertiary-care hospital, and The Miriam Hospital (TMH), an academic community hospital. RIH is the only Level I trauma center in the state, while patients at TMH are primarily community-dwelling older adults.

#### Population

We will recruit 30 participants. These participants will be recruited into six groups with 5 participants each from two different cohorts: cognitively intact and cognitively impaired. Cognitively intact participants will include 20 patients: ages 65-69 (n=5), ages 70-74 (n=5), ages 75-79 (n=5), and ages 80-84 (n=5). Cognitively impaired participants aged 65 years old and older (n=5) will be enrolled with their caregivers (n=5). Caregivers will complete the same tasks as the patient and are encouraged to assist the patient in using the technology. Their perspectives are important for understanding how the technology can be used for communication and to better understand facilitators and barriers of the technology. Quota sampling will be employed to ensure study participants reflect the racial and ethnic diversity of Rhode Island.

#### Eligibility

Eligible participants will be noninstitutionalized, community-dwelling older adults aged 65 years and older who are English-speaking and present to the ED after a fall within the past 7 days. Patients with cognitive impairment, as measured by a score of less than 4 on the Six-Item Screener [17], must have a legally authorized representative available to give informed consent. The patient’s ED physician must intend to discharge the patient after their initial evaluation either to their home or to an assisted living or rehabilitation center. Patients with falls due to syncope, an externally applied force, or critical illness (eg, stroke) will be excluded. Patients who present with altered mental status (eg, intoxicated or agitated), have injuries that prevent mobilization (eg, pelvic or lower extremity fractures), are undomiciled, have allergies to any wearable device component, are unable or unwilling to wear an Apple Watch at home, or have advanced cancer and/or are in hospice care also will be excluded.

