**Objective:**

The goal of this study—the Geriatric Acute and Post-Acute Fall Prevention Intervention (GAPcare) II—is to examine the feasibility, acceptability, and usability of the Apple Watch Series 4 paired with the iPhone and our research app Rhode Island FitTest (RIFitTest) among older adult ED patients seeking care for falls.

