### Field-Testing Nature of the Study

Older adults face unique challenges with using mobile devices, and many studies have shown that interest in using wearables often wanes after initial recruitment [15]. Therefore, we decided we needed to first field-test our protocol among older adults to ensure they would express interest in participating, be able to learn how to use the technology, and stay continuously engaged in the study. A field test is a type of testing that evaluates technology performance in real-world settings. This allows for an enhanced understanding of how the target end user experiences the product and can lead to design optimization and insights into challenges that must still be overcome.

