#### Recruitment and Enrollment

Eligible patients will be approached by a member of the research team and asked if they are interested in participating. If interested, participants will provide written informed consent. Those who consent will answer questions on prior technology use, demographic characteristics, previous falls, and their health history. Participants will receive an Apple Watch Series 4 and an iPhone 7—if they do not already own these devices—for the duration of the study. Participants will be able to use their own Apple Watch and iPhone for the study.

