### Sensor and Survey Data Collection and Analysis

Continuous data collected by the Apple Watch will be sourced from the accelerometer, gyroscope, heart rate monitor, and GPS sensors. Episodic data that will be collected include electronic health record data, fall dairy, Apple Watch measures, RIFitTest app data*,* and the fall-efficacy scale, as outlined in Table 1. This combined data set will then be analyzed descriptively and using longitudinal methods, as appropriate.

Descriptive statistics will be used to measure the following key parameters of feasibility of recruitment, enrollment, participation, and retention [21]: number of patients screened, eligible, and recruited; time required to recruit; number of patients unable to provide consent; number of dropouts; and number of patients with refusal and retention at each follow-up. Frequencies, proportions, rates, means and medians, standard deviations, and other measures of variability will be used to report on these feasibility measures.

Descriptive statistics will also be used to assess the following parameters of acceptability: the fall diary completion rates, days the Apple Watch was worn, and any malfunctions of the Apple Watch or app. We will use the Apple Watch–obtained data to determine the association between gait and fitness measures (eg, step count, stairs climbed, and resting heart rate) and reported falls. To account for the longitudinal nature of this data and within-person correlation, we will use generalized estimating equations or generalized linear models [22].

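### Inability or unwillingness to wear the watch is an exclusion, so refusal at entry leaves the eligible count and recruited-to-eligible is biased upward

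*Protocol article*

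**What the plan says.** The Objective in the abstract is to "examine the feasibility, acceptability, and usability of the Apple Watch Series 4" with its paired phone and study app. The section Field-Testing Nature of the Study explains that the protocol is first tried in older adults "to ensure they would express interest in participating, be able to learn how to use the technology", and to see whether they stay engaged.

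The Eligibility section lists among the exclusions patients who "are unable or unwilling to wear an Apple Watch at home". Recruitment and Enrollment then states: "Eligible patients will be approached by a member of the research team and asked if they are interested in participating".

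Sensor and Survey Data Collection and Analysis names the feasibility counts: "number of patients screened, eligible, and recruited; time required to recruit; number of patients unable to provide consent; number of dropouts", followed by "number of patients with refusal and retention at each follow-up". The process-evaluation row of Table 1 covers numbers screened, agreeing, recruited, treated and retained. Neither place names a count of patients excluded because of the watch.

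Quantitative acceptability is taken from fall diary completion, days of wear, and faults in the watch or app. Qualitative acceptability comes from the interview at the end of participation. Both sources exist only for enrolled people. The Limitations section does not mention this selection.

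**The concern.** Unwillingness to wear the watch at the outset is non-acceptance, and inability to wear it is a feasibility or usability failure. Both are among the answers the field test is meant to give, but the eligibility rule makes their absence a condition of entry. A patient who says no to the device is then classed with patients excluded on clinical grounds, and not with those who were eligible and declined.

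At stake is what the recruitment counts mean. The study is preparation for a later clinical trial, and the article's own Discussion expects reluctance among older adults to take up such devices. If that reluctance shows itself at the bedside, the eligible-to-recruited step will not show it.

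The rule is also hard to apply consistently. Willingness to wear a watch is normally learned by asking, yet the article has only eligible patients asked about interest. The same refusal could be recorded as ineligibility or as a declined approach, and staff at two emergency departments may differ.

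**Working it through.** **The plan's own figures.** The planned sample reproduces: 6 groups × 5 = 30, which is 4 × 5 intact patients + 5 impaired patients + 5 caregivers = 30. It is not affected by this point. The document gives no uptake proportion and no device-refusal rate, so there is no stated figure to recompute. What follows shows direction and a range only.

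**Inputs (all assumed).**
- u: share of patients meeting every other criterion who will not or cannot wear the watch.
- c: share of the remaining patients who consent.

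**Formulas, per 100 otherwise eligible patients.**
- Recruited = c × (100 − u), with u in percent.
- Eligible under the current rule = 100 − u, so recruited/eligible = c, whatever u is.
- Eligible with watch refusers kept in = 100, so recruited/eligible = c × (1 − u), with u as a proportion.
- Overstatement = c − c(1 − u) = c × u. This is zero only when u = 0, and it is never negative.

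**Results with c = 70%.**

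| u | Current rule | Refusers kept in | Overstatement |
|---|---|---|---|
| 10% | 70% | 0.70 × 0.90 = 63% | 7 points |
| 20% | 70% | 0.70 × 0.80 = 56% | 14 points |
| 30% | 70% | 0.70 × 0.70 = 49% | 21 points |
| 40% | 70% | 0.70 × 0.60 = 42% | 28 points |

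**Sensitivity to c.** With c = 80% and u from 10% to 50%, 80% is shown against 72% to 40%, an overstatement of 8 to 40 points. With c = 60% over the same range, 60% is shown against 54% to 30%, an overstatement of 6 to 30 points.

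**Does the screened count recover the answer?** Refusers remain among those screened, so recruited/screened does not lose them. But that denominator also holds patients excluded for syncope, immobilising injury, altered mental status and the other criteria. Without a count specific to the watch, u cannot be separated out.

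**The case against.** The strongest reply is that the study can still find the watch unacceptable. Someone willing at screening may stop wearing it within days. That would show in days worn, diary completion, dropout and the interview, which asks about barriers and reasons for stopping. The article gives waning interest after recruitment as a motive for the field test, and this cohort can measure it. This stands. A reader might infer that the study cannot show low acceptability at all; the document does not support that. Only refusal or inability at entry is hidden.

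Second, uptake is not a named endpoint, and no ratio of recruited to eligible is defined. The plan lists counts. This also stands: a reader might take the percentages above as the error in a planned estimate, but they come wholly from assumed inputs. Nor does the article say that such a proportion will size screening for the later trial. It says the interview findings will improve the app and training. Even so, the eligible count is named as a key parameter, and the rule changes what it contains.

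Third, how staff log a refusal is not described, and such detail may sit in the full protocol. That is fair as to coding. The criterion itself is explicit, though, and following it as written makes the refuser ineligible.

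Fourth, people who will not wear a watch could never supply wear data, so part of the selection is inherent in consent. True; the avoidable part is the label of ineligibility.

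A reader might also look to the age, cognition and race quotas as a further distortion. The article does not say how patients are counted once a cell is full. Any such effect is speculative and would lower the recruited-to-eligible figure, so it is not part of this point.

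**Conclusion.** The concern holds in a limited form. An explicit exclusion conflicts with the stated aim and removes device refusal and inability at entry from the eligible count. Any recruited-to-eligible comparison is then too high whenever such patients exist and are classed as the criterion directs. The direction is certain under that condition, but the size cannot be found from the document. The 7 to 28 points above assume 70% consent among the willing and 10% to 40% who will not wear the watch.

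Measures after enrolment remain valid for what they cover: people who had already agreed to wear the watch. The planned 30 participants and the procedures are unaffected. The change is worth making because the distortion bears on part of the study's own question and is cheap to remove.

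**What to change.** - Remove from the exclusions the clause covering patients who "are unable or unwilling to wear an Apple Watch at home".
- Count patients who meet all other criteria as *eligible, declined device* or *eligible, unable to use device*. Keep the two apart, since refusal bears on acceptability and inability on feasibility and usability.
- Report recruitment with both groups in the denominator, and report each as its own count at entry.
- State in the Limitations that wear-time and interview results apply to people willing to wear the watch.
- Recruitment began in December 2019, so re-code patients already screened where the reason was recorded. Where it was not, say that the early counts cannot be corrected.

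**Cost.** A change to the eligibility wording and two screening codes. No added patients or visits, and nobody is made to wear a watch, because consent already governs that. The downside is a less favourable recruitment proportion.

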#### Recruitment and Enrollment

Eligible patients will be approached by a member of the research team and asked if they are interested in participating. If interested, participants will provide written informed consent. Those who consent will answer questions on prior technology use, demographic characteristics, previous falls, and their health history. Participants will receive an Apple Watch Series 4 and an iPhone 7—if they do not already own these devices—for the duration of the study. Participants will be able to use their own Apple Watch and iPhone for the study.

#### Apple Watch Specifications and Deployment

For this study, each participant will use the Apple Watch Series 4 (GPS), manufactured by Quanta Computer Compal Electronics. We will use the Apple Watch with the larger 44-mm watch face and Velcro wrist strap to make it easier to use for older adults with vision impairment or those lacking fine motor skills.

#### ED Procedures

The following steps will be taken for device setup *prior* to patient approach:

Charge and pair the Apple Watch and iPhone via Bluetooth; for participants with their own devices, pairing will occur in real time.Maximize font and icon size on both devices to enhance readability.Set brightness at its maximum to improve readability.Delete irrelevant content and minimize notifications (eg, remove and mute unnecessary apps and notifications, respectively) to limit distractions.Download the RIFitTest app from the Apple App Store onto the iPhone.Add the study principal investigator and an emergency contact to the contact list to receive fall alert notifications.

Training in the use of the iPhone, Apple Watch, and RIFitTest app as well as study-related activities will also be provided, including the following:

iPhone and Apple Watch setup instructions, including how to turn the device on and off, unlock and set a password, and charge both devices.Real-time demonstration of *active tasks* accessed through the study app.A demonstration of how to log a fall and/or injury through the app.Education in the research protocol, including when to use the Apple Watch (ie, continuously, including while bathing and participating in water activities), nightly charging of iPhone, mealtime charging of the Apple Watch, daily completion of fall surveys, and weekly completion of *active tasks* on the RIFitTest app.Orientation to the study materials: file, business card with hotline for assistance, technology manual (see Multimedia Appendix 1), calendar of assessment timing, technology agreement, and consent form.

Figure 1 illustrates a timeline of the study that will be explained to participants.

**Figure 1 figure1:**
[figure not shown]
Timeline of study duration. ED: emergency department; GAPcare II: Geriatric Acute and Post-Acute Fall Prevention Intervention II; RA: research assistant.

#### Follow-up Procedures

Study participation will last for 30 days or until the participant is no longer able or willing to participate. All participants will be contacted by research staff on days 3, 8, 15, and 22 to remind them to complete the steps in the study protocol and to answer questions. Participants will take part in a 30-minute semistructured interview at the completion of the study period. The interview will be conducted by the principal investigator and her staff. The intent of the interview will be to record participants’ experience with the study as well as to provide information on the feasibility, usability, and acceptability of the Apple Watch, iPhone, and RIFitTest app. Participant feedback about the quality of the intervention materials will also be solicited. The information collected in the interview will be used to improve the app and training procedures in preparation of the subsequent clinical trial.

#### Measures

There are five data sources that will contribute data for this field test: research staff–administered surveys, qualitative interviews with patients and caregivers, Apple Watch sensor-obtained measures, user-completed iPhone surveys (ie, a digital fall diary, fall efficacy survey, and a usability survey), and user-completed *active tasks* (ie, guided motor and cognitive assessments). Specific measures are summarized in Table 1.

**Table 1 table1:** Study instruments, surveys, and active tasks.

Instrument			Description	Administration time
**Process evaluation**				
	**Research staff–administered survey**			
		Screening, eligibility, and retention	This survey will record how many patients were screened, agreed to participate, were recruited, received intended treatment, and were retained.	Baseline and 30 days
**Outcome evaluation**				
	**Research staff–administered surveys and interviews**			
		Enrollment questionnaire	Demographic characteristics Prior fall history, comorbidities, emergency department index visit fall circumstances, and injuries	Baseline; <5 minutes
		Six-Item Screener [17]	6-point questionnaire to measure cognitive impairment for study screening; <4 indicates high risk for cognitive impairment	Baseline; 2 minutes
		Qualitative interviews	These interviews will track follow-up phone sessions with research staff. Interviews record participants’ experience with the study while also establishing an understanding of the usability of both the Apple Watch and RIFitTest^a^ app for older adults. The timing and length of each session and barriers to attendance are recorded.	Days 3, 8, 15, 22, and 30
	**Apple Watch sensor-obtained measures**			
		Apple Watch measures (ie, accelerometer, gyroscope, and physiological sensors)	Gait and fitness (ie, time spent walking, standing, and climbing steps; 4-meter walk gait speed test; and resting heart rate) Data will include cognitive and active task performance, including cadence and walking speed related to their gait and balance and Stroop test. Performance reports will be generated for each participant.	Baseline ± continuously (days 1 to 30)
	**User-completed iPhone surveys**			
		Fall diary	Daily app-based entry that will ask participants if they have fallen	Days 1 to 30
		Fall-efficacy survey	Measure of fear of falling, which increases fall risk	Days 1 and 28
		Usability survey	This survey will record each participant’s experience with the app, as well as with the active and cognitive tasks.	Days 7 and 28
	**User-completed *active tasks* [12] on the iPhone**			
		Gait and balance test	Active task; measure of 20 steps of walking in one direction, returning, and then standing still for 30 seconds	Days 1, 7, 14, 21, and 28
		Timed walk	Measure of a walking distance of 109 yards in a straight line as quickly as possible	Days 1, 7, 14, 21, and 28
		Stroop test	Measure of ability to quickly identify color of text	Days 1, 7, 14, 21, and 28
		Reaction time test	Active task; measure of speed at clicking a button when shown	Days 1, 7, 14, 21, and 28
		Trail-making test	Active task; measure of ability to follow an alphanumeric sequence (1...A...2...B..., etc)	Days 1, 7, 14, 21, and 28

^a^RIFitTest: Rhode Island FitTest.

### Qualitative Interviews

#### Interview Procedure

Study staff will conduct interviews with both the participants and their caregivers, when applicable. They will use an interview guide containing semistructured questions with follow-up questions and probes to explore participants’ responses.

#### Recording

Interviews will be transcribed and deidentified. Transcripts will be corrected for accuracy as needed using the audio recording.

#### Analysis

We will use *framework analysis*—a qualitative analysis technique, in which investigators summarize content within categories into charts after transcription [18,19]—as it is particularly well-suited to generate recommendations within a limited time period, so as to inform the subsequent clinical trial. Another benefit of the framework method is the emphasis on transparency in data analysis and the links between the stages of the analysis [19]. Framework methods include summarizing qualitative data into a matrix or spreadsheet where data are entered by codes (columns) and cases (rows) [20]. Specifically, we will take the following steps:

Read and re-read the transcripts to note initial observations; iteratively search for common themes, subthemes, and patterns across participant responses; and develop a coding matrix and assign data to the themes and categories in the coding matrix.Review themes in relation to the extracts and entire data set; identify associations between the themes until a “whole picture” is apparent.Select representative quotes from the interviews to illustrate the themes.Record ideas about emerging themes in an ongoing audit trail.Prepare the analytic narrative and contextualize it using existing research on this topic.

#### Debriefing

Interviewers will complete a debriefing form after the interview to document the following: (1) tone of interview, (2) agenda adherence, (3) interview description, (4) major themes, (5) lessons learned, (6) question strategies, and (7) saturation.

#### Poststage Interview Content

The following three study aims will be addressed through qualitative data collected during the poststage interview:

Feasibility: (1) ability to carry out device charging, application, and manipulation; (2) barriers to daily use; and (3) responses to specific planned components of the intervention.Acceptability: receptivity to and concerns about device use.Usability: (1) prior experiences with wearables; (2) trajectories of use, including reasons for continuation or cessation of use; (3) quality of in-person and telephone device support and training; (4) connectivity to smartphone and Wi-Fi, if desired; (5) caregiver experiences; and (6) patient and caregiver’s perceived needs and preferred method of use.

Interview questions will be grounded in the four constructs of the UTAUT model.

### Sensor and Survey Data Collection and Analysis

Continuous data collected by the Apple Watch will be sourced from the accelerometer, gyroscope, heart rate monitor, and GPS sensors. Episodic data that will be collected include electronic health record data, fall dairy, Apple Watch measures, RIFitTest app data*,* and the fall-efficacy scale, as outlined in Table 1. This combined data set will then be analyzed descriptively and using longitudinal methods, as appropriate.

Descriptive statistics will be used to measure the following key parameters of feasibility of recruitment, enrollment, participation, and retention [21]: number of patients screened, eligible, and recruited; time required to recruit; number of patients unable to provide consent; number of dropouts; and number of patients with refusal and retention at each follow-up. Frequencies, proportions, rates, means and medians, standard deviations, and other measures of variability will be used to report on these feasibility measures.

Descriptive statistics will also be used to assess the following parameters of acceptability: the fall diary completion rates, days the Apple Watch was worn, and any malfunctions of the Apple Watch or app. We will use the Apple Watch–obtained data to determine the association between gait and fitness measures (eg, step count, stairs climbed, and resting heart rate) and reported falls. To account for the longitudinal nature of this data and within-person correlation, we will use generalized estimating equations or generalized linear models [22].

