**Methods:**

We will conduct field-testing with older adult ED patients (n=25) who sustained a fall and their caregivers (n=5) to determine whether they can use the Apple Watch, iPhone, and app either (1) continuously or (2) periodically, with or without telephone assistance from the research staff, to assess gait, fitness, and/or falls over time. During the initial encounter, participants will receive training in the Apple Watch, iPhone, and our research app. They will receive an illustrated training manual and a number to call if they have questions about the research protocol or device usage. Participants will complete surveys and cognitive and motor assessments on the app during the study period. At the conclusion of the study, we will solicit participant feedback through semistructured interviews. Qualitative data will be summarized using framework matrix analyses. Sensor and survey response data will be analyzed using descriptive statistics.

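### A generalized linear model, as named, does not account for within-person correlation, so one of the two methods offered for the sensor–falls association misses its stated purpose

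*Protocol article*

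**What the plan says.** The section Sensor and Survey Data Collection and Analysis promises in general terms that "This combined data set will then be analyzed descriptively and using longitudinal methods, as appropriate". It assigns descriptive statistics to the feasibility and acceptability measures. It then states one inferential aim, to "determine the association between gait and fitness measures (eg, step count, stairs climbed, and resting heart rate) and reported falls", and follows it directly with the model statement: "To account for the longitudinal nature of this data and within-person correlation, we will use generalized estimating equations or generalized linear models".

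The data are repeated daily. Under Follow-up Procedures, "Study participation will last for 30 days or until the participant is no longer able or willing to participate", and Table 1 describes the fall diary as "Daily app-based entry that will ask participants if they have fallen", for days 1 to 30. Under Population, "These participants will be recruited into six groups with 5 participants each from two different cohorts": 20 cognitively intact patients, 5 cognitively impaired patients and 5 caregivers.

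**The concern.** The model sentence gives a purpose and two methods joined by *or*. The first method meets the purpose. The second, as named, assumes independent observations. It handles within-person correlation only if it is extended, usually to a mixed model or with a variance clustered on the person, and the sentence names neither extension. An analyst could follow the text exactly, fit a plain GLM to as many as 25 × 30 = 750 patient-days, and ignore the correlation that the sentence sets out to handle.

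The cost would be confidence intervals that are too narrow, and too many apparent associations between activity measures and falls, in a study meant to inform a later clinical trial. This is not a detail left to an analysis plan. The article states the method, and the statement does not match its own aim.

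**Working it through.** **No plan figure to reproduce.** The article gives no significance level, ICC or standard error for this analysis. The only count that can be checked is the sample: 4 × 5 + 5 + 5 = 30, which agrees.

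**Inputs.** Days per person: m = 30 (Follow-up Procedures; Table 1). Patients: 25 (Abstract, Methods; Population). The ICC of the sensor measure (ICC_x) and of the daily fall report (ICC_y) are assumptions, shown as ranges.

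**Formula.** With 30 records per person and exchangeable correlation in both variables, ignoring the clustering understates the variance of the slope by the factor

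V = 1 + (m − 1) × ICC_x × ICC_y = 1 + 29 × ICC_x × ICC_y.

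The naive standard error divided by the true one is 1/√V. The actual size of a nominal 5% test is 2 × (1 − Φ(1.96/√V)).

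**Results at ICC_x = 0.5**, a measure that varies both between people and from day to day:

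| ICC_y | V | naive SE / true SE | actual size |
|---|---|---|---|
| 0.01 | 1.15 | 0.94 | 6.7% |
| 0.05 | 1.73 | 0.76 | 13.6% |
| 0.10 | 2.45 | 0.64 | 21% |
| 0.30 | 5.35 | 0.43 | 40% |

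**Bounds.** At ICC_x = 0 (purely within-person variation), V = 1 and the size stays at 5% for every ICC_y. At ICC_x = 1 (a covariate constant within person), V is 1.29, 2.45, 3.9 and 9.7 for the same four values of ICC_y, and the size is 8.4%, 21%, 32% and 53%.

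**How common are falls?** The Introduction cites 31% falling again within 6 months. At a constant rate, which is an assumption, that is −ln(0.69)/182.5 = 0.0020 per day. The 30-day probability is 1 − 0.69^(30/182.5) = 5.9%, or 25 × 0.059 ≈ 1.5 fallers among the 25 patients. A daily event this rare has a small ICC_y unless the risk is concentrated in very few people.

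**Simulation under no association.** 25 people × 30 days, logistic model with a random intercept, ICC_x = 0.5, 400 attempts per setting. Runs with fewer than 3 falls were dropped. The GEE used an independence working correlation and an uncorrected robust variance.

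| Falls per day | Intercept SD | ICC_y | Usable runs | GLM SE ratio | GLM size | GEE SE ratio | GEE size |
|---|---|---|---|---|---|---|---|
| 0.2% | 1 | 0.003 | 91 | 0.97 | 6.6% | 0.77 | 14.3% |
| 1% | 1 | 0.016 | 386 | 0.91 | 4.1% | 0.79 | 14.8% |
| 1% | 2 | 0.11 | 344 | 0.76 | 14.8% | 0.63 | 25.3% |
| 5% | 1.5 | 0.13 | 400 | 0.67 | 17.2% | 0.85 | 10.8% |
| 20% | 1.5 | 0.25 | 400 | 0.47 | 33.0% | 0.88 | 9.2% |

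The first row is rough: with 91 runs, the Monte Carlo standard error of a 5% rate is √(0.05 × 0.95/91) = 2.3 percentage points. In the third and fourth rows the formula gives SE ratios of 0.62 and 0.58, so it somewhat overstates the shortfall there. The GLM shortfall is slight at the background rate and becomes large only when falls are more frequent or strongly concentrated in a few people.

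**The case against.** The strongest reply is that the sentence declares the right aim, names GEE first, and sits in a section that promises longitudinal methods. In a condensed article, *generalized linear models* may be shorthand for the mixed-model version. That is plausible, but the word that would make it so is absent, so the text needs correcting on either reading. What stands is that nothing commits the study to a plain GLM, and harm arises only if that option is taken unextended.

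A reader might infer that standard errors will be far too small, by a factor of 1.6 to 3.1. Those factors are √2.45 and √9.7. They require a covariate constant within person and an outcome ICC of 0.05 to 0.30. The article's examples (steps, stairs, resting heart rate) are sensor measures that can change from day to day, and falls are probably rare. The factors therefore do not describe the analysis stated. In the other direction, the Introduction says that recurrence risk is highest soon after the emergency visit, so the constant-rate figure may be too low for these 30 days.

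A reader might also extend the problem to diary completion or to trends in active-task scores. Diary completion is assigned to descriptive statistics, and no trend test on active tasks is stated. The Limitations section also says that the sample is not sized for cognitive and motor trajectories.

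Finally, the absence of a small-sample variance correction for GEE, or of clustering on patient–caregiver pairs, might be read as an error. An article commonly leaves such details to the full protocol or analysis plan, which are not shown. The simulation does show that an uncorrected robust variance can perform poorly with 25 clusters, so this is useful advice but not a separate fault.

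**Conclusion.** The point holds as a correction of the method statement. One of the two options, as named, does not account for within-person correlation. Used without extension, it would understate standard errors whenever the sensor measure and falls both cluster positively within person.

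The size cannot be fixed from the article. At an assumed covariate ICC of 0.5 it runs from negligible to a test size of about 40%, over assumed outcome ICCs of 0.01 to 0.30. At the article's own background fall rate, spread evenly, it is probably small. At that rate, too few falls is a more serious limit than the choice of model.

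Severity is minor to moderate. This is a secondary analysis in a 30-person field test whose aims are feasibility, acceptability and usability, and the Abstract describes the sensor and survey analysis as descriptive. The main results do not depend on it.

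**What to change.** Replace *generalized linear models* in that sentence with *generalized linear mixed models with a participant random intercept*. Alternatively, delete the second option and keep only GEE clustered on participant. It is better to choose one: for a binary outcome the two estimate different quantities (conditional on the person, or averaged over people), so they are not interchangeable.

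As supporting advice, if GEE is kept with about 25 to 30 clusters, use a small-sample-corrected variance (Kauermann–Carroll or Mancl–DeRouen) with a t reference. If caregivers enter the model, cluster on the pair.

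The cost is one phrase and standard software options. Intervals become wider, only slightly so if clustering is weak. The change will not rescue the analysis if only one or two patients fall, since the association may then not be estimable by any of these models.
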